### Data management

Participant clinical data and demographic information will be initially recorded in the electronic medical record systems at participating sites. Relevant study data will then be transferred into REDCap databases hosted on secure, password-protected servers at Austin Health. Data from each site will be stored locally, with a master database maintained centrally at Austin Health for analysis.

All data related to this study will be retained for 15 years after study completion, in accordance with institutional policies, after which all electronic records will be securely destroyed.

Only aggregated, non-identifiable data will be presented in publications and reports.

### Adverse events

AEs in this study are categorised as immune-mediated, non-immune-mediated or serious AEs.

Immune-mediated AEs are defined as symptoms consistent with an IgE-mediated allergic reaction occurring during or within 48 hours of the OFC. These may include, but are not limited to, cutaneous symptoms such as urticaria or angioedema, gastrointestinal symptoms such as vomiting or diarrhoea, or respiratory symptoms consistent with anaphylaxis. Such events will be classified according to criteria outlined in the PRACTALL guidelines and will be adjudicated by two independent reviewers, with a third reviewer as a tie-breaker where necessary.^9^

Non-immune-mediated AEs refer to symptoms that are not indicative of IgE-mediated allergy and do not meet criteria for a serious AE. Examples include taste aversion or anxiety leading to discontinuation of the challenge, nausea or gastrointestinal discomfort unrelated to an allergic mechanism. These will also be assessed within 48 hours of the food challenge.

A serious adverse event is defined as any untoward medical occurrence that, in the opinion of the independent adjudicators, is causally related to the food challenge and results in one or more of the following outcomes: death; life-threatening reaction; inpatient hospitalisation; persistent or significant disability or incapacity or an event requiring intervention to prevent permanent impairment or damage.

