### Outcomes

The primary outcome is the safety of home-based OFC, measured by the proportion of participants who experience an immune-mediated AE during the food challenge. Immune-mediated AEs are defined as symptoms indicative of an IgE-mediated hypersensitivity reaction to the challenge food, as defined by the PRACTALL guidelines.^9^ AEs will be reviewed to determine the severity and causality (immune-mediated vs non-immune-mediated) by an independent panel consisting of two allergy specialists from non-participating sites. In the event of discordant assessment between the two allergists, the decision will be passed onto a third clinician.

In addition to the primary safety outcome, the study will assess a range of secondary outcomes evaluating recruitment feasibility, protocol adherence and the occurrence of non-immune mediated AEs (Box 2). These measures will help determine whether home-based challenges are practical and acceptable in routine clinical practice. Furthermore, exploratory outcomes will investigate patient-reported quality of life, rates of sustained food reintroduction and potential health economic impacts, providing insights into the broader clinical and societal implications of adopting home food challenges.

Box 2Secondary and exploratory outcomes
*Secondary outcomes*
Secondary outcomes include:Proportion of participants who experience non-immune-mediated adverse events during the food challenge, including:Taste aversionAnxiety preventing completion of the challenge.Feasibility outcome measures:Eligibility to screened ratio (*proportion of screened patients who meet eligibility criteria*).Recruitment to eligibility ratio (*proportion of eligible patients willing to participate*).Intervention to recruitment ratio (*proportion of recruited patients who complete oral food challenge*).Identification of barriers to protocol completion in the home challenge arm, assessed through participant interviews.Protocol compliance in both study arms.Utility outcome:Proportion of participants identified as tolerant to the implicated food after challenge.
*Exploratory outcomes*

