### Sample size and statistical analysis

A total of 120 participants (60 per arm) will be recruited for this pilot trial. This sample size will provide estimates of safety and recruitment feasibility outcomes with a precision of <20% (total width of CIs). The chosen sample size is also considered sufficient to generate reliable estimates of safety and potential efficacy for planning a future definitive trial, as precision gains diminish beyond approximately 60 participants per group for binary outcomes.^15^

All analyses will follow the intention-to-treat principle, with supplementary per-protocol analyses conducted for sensitivity. Continuous variables will be summarised as medians with IQRs, while categorical variables will be presented as frequencies and percentages.

Binary outcomes will be presented as counts and proportions with exact 95% CIs. Comparative analyses between study arms will report absolute risk differences and relative risks, each with 95% CIs, using generalised linear models with a binomial family and identity or log link functions as appropriate.

No interim analyses are planned for this pilot study. Missing data are expected to be minimal and, where necessary, will be described in reporting.

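### The non-immune AE definition excludes serious events, so the Box 2 non-immune proportion omits its most severe cases and disagrees with the adjudication split under Outcomes

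*Protocol article*

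**What the plan says.** The Adverse events section opens with three categories: "AEs in this study are categorised as immune-mediated, non-immune-mediated or serious AEs". It then defines each one.

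- **Immune-mediated:** "Immune-mediated AEs are defined as symptoms consistent with an IgE-mediated allergic reaction occurring during or within 48 hours of the OFC". Nothing here depends on seriousness.
- **Non-immune-mediated:** "Non-immune-mediated AEs refer to symptoms that are not indicative of IgE-mediated allergy and do not meet criteria for a serious AE". This definition carries a seriousness exclusion.
- **Serious:** "any untoward medical occurrence that, in the opinion of the independent adjudicators, is causally related to the food challenge", together with one of a list of outcomes that includes inpatient admission. A causal link to the challenge is required, but an IgE mechanism is not.

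The Outcomes section uses the first two categories as endpoints. The primary outcome is "measured by the proportion of participants who experience an immune-mediated AE during the food challenge". The first secondary outcome in Box 2 is "Proportion of participants who experience non-immune-mediated adverse events during the food challenge". No primary, secondary or exploratory outcome counts serious AEs.

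Outcomes also describes the adjudication: "AEs will be reviewed to determine the severity and causality (immune-mediated vs non-immune-mediated) by an independent panel". That is a two-way split by mechanism with severity as a separate judgement, and no third group is set aside for serious events.

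**The concern.** Mechanism and seriousness are two different properties of an event, and the Adverse events section mixes them in one classification. It does so on one side only: a serious IgE-type reaction stays in the immune-mediated group, whereas a serious non-IgE event leaves the non-immune group.

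The non-immune proportion is one of only two AE-based outcomes in a trial meant to supply preliminary safety data for home challenge. Under the literal definition, a participant whose challenge ended early because of taste aversion counts as an event. A participant admitted to hospital with a challenge-related, non-IgE event, and with no other AE, does not. The same numerator feeds the exact confidence interval for each arm and the planned between-arm risk difference and relative risk, so the omission would carry into all of them.

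The article also gives two different answers for the same event: the wording under Outcomes would count it as non-immune, and the wording under Adverse events would not.

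**Working it through.** **Step 1. Apply the definitions to each type of challenge-related event.** The inputs are the three definitions under Adverse events and the two AE outcomes under Outcomes and Box 2. Box 2 is assumed to use the term as the Adverse events section defines it.

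| Event | Primary (immune) | Box 2 (non-immune) | Serious-AE category |
|---|---|---|---|
| IgE-type, not serious | counted | no | no |
| IgE-type, serious | counted | no | yes |
| Not IgE-type, not serious | no | counted | no |
| Not IgE-type, serious | no | **not counted** | yes |

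Only the last row falls outside both listed AE outcomes. The second row shows that the three categories already overlap for IgE-type reactions, so the exclusion is not needed to keep them separate.

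**Step 2. Apply the two-way split under Outcomes to the last row.** The event is adjudicated as immune or non-immune. It is not IgE-type, so it is non-immune and would count in Box 2. The two sections therefore give different numerators for one outcome.

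**Step 3. Check a neighbouring case.** The serious-AE definition requires a causal link to the challenge. A serious non-IgE event judged unrelated does not meet it. If that event presents as symptoms within the 48-hour window, it can still count as non-immune-mediated, while the related event cannot.

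**Step 4. Size.** The article gives no figure for these events to reproduce. Its only numerical claim about safety proportions is a total interval width below 20%. Exact widths reach at most 18.5% with 120 participants. In one arm of 60 they stay below 20% up to 9/60 (19.5%) and exceed it at 10/60 (20.2%). The present point does not depend on that claim.

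The sample size section states: "A total of 120 participants (60 per arm) will be recruited for this pilot trial". One omitted participant changes an arm's proportion by 1/60 = 1.67 percentage points.

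Take an arm in which that participant has the only non-immune event, and use the exact (Clopper-Pearson) interval that the plan specifies:

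- Event omitted, 0/60 = 0%. The upper limit is 1 − 0.025^(1/60) = 5.96%, so the 95% interval is 0 to 5.96%.
- Event counted, 1/60 = 1.67%. The lower limit is 1 − 0.975^(1/60) = 0.04%. The upper limit solves (1 − p)^60 + 60p(1 − p)^59 = 0.025, which gives p = 8.94%. The 95% interval is 0.04 to 8.94%.

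The reported upper limit would be 5.96% where 8.94% applies, a difference of 2.98 percentage points.

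**The case against.** The strongest reply is that nothing is lost. The event falls in the serious-AE category, it is assessed by independent adjudicators, and a table of serious AEs by arm is something an article may leave to the full protocol or analysis plan. This stands as far as it goes. A reader might infer that the participant vanishes from the trial's safety record, and the article does not support that. What remains is that the article states a rule, rather than leaving out a detail, and the rule removes these events from a named secondary outcome. A separate serious-AE table would not change that proportion.

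A second reply is that the adjudication wording under Outcomes already separates mechanism from severity, so the literal exclusion might never be applied. This is partly right, although severity and seriousness are not the same thing. It supports treating the point as a conflict between two sections, to be settled before adjudication.

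A third reply is that such events should be very uncommon. The exclusion criteria remove histories inconsistent with IgE-mediated reactions and conditions that would raise risk, and the article's own examples of non-immune events are mild. This also stands. The article gives no rate, so no probability of seeing such an event can be derived from it.

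Two stronger readings are tempting. Because the opening sentence lists three categories joined by "or", a reader might infer that serious IgE-type reactions also leave the primary outcome. The immune-mediated definition contains no such exclusion, so this does not follow. A reader might also infer that the arm with more serious events must show the lower non-immune proportion. That would depend on how non-serious events are distributed between the arms and on whether the affected participants had another, non-serious AE.

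**Conclusion.** The point holds as a narrow but real definitional error. As written, the non-immune AE proportion in Box 2 leaves out serious, challenge-related, non-IgE events, and this conflicts with the two-way adjudication split under Outcomes. The primary outcome is unaffected, and the omitted events are still recorded as serious AEs, although serious AEs are not a listed outcome.

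The expected numerical effect is small because such events should be rare. Per event it is 1.7 percentage points in an arm of 60. In the example of a single event, the exact upper limit reads 6.0% instead of 8.9%. These figures assume that the exclusion is applied literally, that all 60 participants are in the denominator, and that the affected participant has no separate non-serious, non-immune AE. The finding itself rests on the definitions and not on any assumed event rate.

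**What to change.** 1. In the Adverse events section, delete the final clause of the non-immune-mediated definition, the one that excludes events meeting serious-AE criteria. The definition then agrees with the split under Outcomes.
2. Reword the opening sentence of that section so that mechanism (immune or non-immune) is the classification and seriousness is an attribute that any event can have. Have the adjudicators record the two separately for every event.
3. State that the Box 2 proportion counts all non-immune-mediated events, serious or not.

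The cost is one deleted clause, small wording changes and one field on the adjudication form. No additional participants, visits or assessments are needed, and clinical management does not change. The only downside is that the reported non-immune proportion may be slightly higher. The change should be made before adjudication begins, so that where a serious event counts is not decided once the event is known.

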### Randomisation

Eligible participants will be randomised in a 1:1 ratio to either the intervention arm (home-based food challenge) or the control arm (standard in-clinic food challenge). Randomisation will be performed using a permuted block design, stratified by hospital site, participant gender and evidence of prior sensitisation to the challenge food, to ensure balanced allocation across study arms.

The randomisation sequence will be generated in Stata and delivered through REDCap (Research Electronic Data Capture), hosted on secure servers at Austin Health. Allocation concealment will be ensured until the point of randomisation. Investigators and participants will not be blinded to group assignment due to the nature of the intervention.

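### Relatedness is built into the SAE definition, so serious events judged unrelated are not SAEs and are either counted as non-immune AEs or not classified at all

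*Protocol article*

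**What the plan says.** The Adverse events section of the protocol article sets up three categories: "AEs in this study are categorised as immune-mediated, non-immune-mediated or serious AEs". They are defined in different ways.

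- **Immune-mediated AEs** are defined by IgE-type symptoms during the challenge or in the 48 hours around it. Seriousness plays no part.
- **Non-immune-mediated AEs** are defined partly by exclusion: "Non-immune-mediated AEs refer to symptoms that are not indicative of IgE-mediated allergy and do not meet criteria for a serious AE". The illustrations are minor: "Examples include taste aversion or anxiety leading to discontinuation of the challenge, nausea or gastrointestinal discomfort unrelated to an allergic mechanism". The window is the same: "These will also be assessed within 48 hours of the food challenge".
- **Serious AEs** need two things at once. The event must be one that, "in the opinion of the independent adjudicators, is causally related to the food challenge and results in one or more of the following outcomes", and a list of outcomes from death to intervention against permanent damage follows.

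Under Outcomes, the panel's task is described differently: "AEs will be reviewed to determine the severity and causality (immune-mediated vs non-immune-mediated) by an independent panel". Box 2 lists the proportion with non-immune-mediated AEs as a secondary outcome. SAEs are not listed as an outcome there or elsewhere. No section of the article provides for a count of serious events regardless of cause.

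**The concern.** Seriousness describes what happened to the participant; relatedness is an opinion about why. The article merges them, so the SAE count cannot be read without knowing how the adjudicators attributed each event, and a serious event that they set aside does not appear as serious anywhere.

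The non-immune definition excludes whatever meets the SAE criteria, so the same causality opinion also decides what enters that secondary outcome, and it does so in an odd direction. A related serious non-IgE event is kept out, and an unrelated one is let in. A reader of the results would see the unrelated event tabulated with taste aversion and anxiety, or would not see it.

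At stake are the SAE tabulation and one secondary outcome, in a pilot whose safety data are meant to inform a larger non-inferiority trial.

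**Working it through.** The article states no SAE rate or count, so there is no figure to reproduce. The check is to apply its definitions, as written, to an event that has one of the listed serious outcomes.

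| Symptoms | Judged related to challenge? | Timing | Result under the current text |
|---|---|---|---|
| IgE-type | Yes | Within 48 h | SAE, and eligible as immune-mediated |
| IgE-type | No | Within 48 h | Not an SAE; immune-mediated status is decided without reference to the SAE rule |
| Not IgE-type | Yes | Within 48 h | SAE; excluded from non-immune AEs |
| Not IgE-type | No | Within 48 h | Not an SAE; meets the non-immune definition |
| Any | Yes | After 48 h | SAE (the SAE definition carries no window) |
| Any | No | After 48 h | No category |

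Rows 3 and 4 differ only in the causality opinion, yet they exchange places between the SAE count and the secondary outcome. Row 6 is a gap of the same kind. Rows 1 and 2 show that the primary outcome does not pass through the SAE definition.

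**Who decides.** Outcomes gives the panel severity and the immune versus non-immune distinction. Relatedness to the challenge is a further question: a non-immune event may or may not be caused by the challenge. It appears only under Adverse events, yet it determines whether an SAE exists.

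**Time at risk by arm.** Treatment arms gives daily home dosing over 5 days and a clinic challenge lasting several hours. If the window runs from the first dose to 48 hours after the last, the home arm is observed for about 4 + 2 = 6 to 5 + 2 = 7 days, and the clinic arm for a little over 2 days. Coincidental events have more time to occur in the home arm. The evidence for judging relatedness also differs, because clinic doses are directly supervised and most home doses are not.

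**Scale.** Exact (Clopper-Pearson) 95% limits with n = 60 per arm, from Sample size and statistical analysis. For x = 0 the upper limit is 1 − 0.025^(1/60) = 0.0596. For x > 0 the limits are the 0.025 quantile of Beta(x, n − x + 1) and the 0.975 quantile of Beta(x + 1, n − x).

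| Events in 60 | Estimate | 95% limits |
|---|---|---|
| 0 | 0.0% | 0.0% to 6.0% |
| 1 | 1.7% | 0.04% to 8.9% |
| 2 | 3.3% | 0.4% to 11.5% |

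The counts of 0 to 2 are assumed. The table shows what one causality call can do to an arm's SAE proportion. It does not estimate how often such a call will arise.

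**The case against.** The strongest reply is that the rule, followed exactly, counts challenge-related SAEs. That is a narrower quantity, not a false one, and the article nowhere promises an all-cause count. This stands as far as it goes, but it does not explain why the non-immune outcome should take in unrelated serious events and leave out related ones.

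Other limits also stand. The affected events must be serious, judged unrelated, and either non-IgE within 48 hours or later. Box 2 counts non-immune AEs during the challenge, which may be narrower than 48 hours. Participants are selected as low-risk, so few such events should be expected. The limits for 0 to 2 of 60 would apply to any binary event.

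A reader might infer that the primary safety result is compromised. The documents do not support this: the immune-mediated definition neither uses nor excludes SAE status.

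A reader might also infer that home-arm serious events will be selectively removed, because home doses are largely unobserved and, under Randomisation, "Investigators and participants will not be blinded to group assignment due to the nature of the intervention". That does not follow either. Relatedness is judged by specialists from non-participating sites, with a third clinician for disagreements. Whether the panel is blinded is not stated. The first home-arm dose is supervised, with 60 minutes of observation. The longer home dosing period could equally add coincidental events to that arm. Differential attribution is possible; its direction is not established.

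Nor does the article show that reporting of serious events must wait for adjudication. Reporting procedures commonly sit in the full protocol, which is not shown.

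**Conclusion.** The point holds in a limited form. As written, the SAE definition makes seriousness conditional on relatedness. An unrelated serious event that is not IgE-type and falls within 48 hours is then a non-immune AE, an equivalent related event is excluded from that category, and an unrelated event falling later is not classified.

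The effect is confined to the SAE count and the secondary non-immune outcome. The number of events is probably small, but at 60 per arm a single call matters to the tabulation: moving from 0 to 1 event raises an arm's upper limit from 6.0% to 8.9%. No change in sample size follows.

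This rests on reading the three categories as the whole classification, as the article presents them, and on illustrative event counts. It is worth correcting because it is a stated rule rather than omitted detail, and because correcting it loses nothing.

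**What to change.** In the Adverse events section:

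1. Define an SAE by the listed outcomes alone, whatever the cause.
2. Record relatedness to the challenge and immune or non-immune mechanism as two separate adjudicated fields, and align the description of the panel's task under Outcomes.
3. Report by arm both all SAEs and SAEs judged related.
4. Keep the closing exclusion in the non-immune definition ("symptoms that are not indicative of IgE-mediated allergy and do not meet criteria for a serious AE"). With an outcome-based SAE definition, it keeps every serious non-IgE event out of that secondary outcome. Deleting it would let them all in.

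The cost is a wording change and an added field in the REDCap database. The downside is that a few unrelated events will appear in the SAE table, possibly more in the home arm because its dosing period is longer. The related-SAE count should therefore stand beside the all-SAE count. Because related SAEs are what the present definition counts, that information is retained.

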### Withdrawals and stopping criteria

Participants may withdraw from the study at any time without providing a reason. Data collected prior to withdrawal may be included in the final analyses unless the participant specifically requests that their data be destroyed and it has not yet been incorporated into the analysis. No participants who withdraw after randomisation will be replaced.

